### Secondary outcomes—safety

AEs experienced during treatment (not associated with the underlying trauma).Significant changes in physiological parameters or sedation scores during treatment.Evaluation of AEs at 14 ± 2 days following ED discharge using a follow-up questionnaire that includes high-output nephrotoxicity.

### Screening

Screening commences once a child is registered in the ED with minor trauma, defined as “a non-critical and non-limb threatening physical wound or injury of the tissues”; this definition includes soft tissue injuries, fractures or ligament injuries of the extremities, burns, penetration by foreign bodies, lacerations, dislocation and contusions. Trial research nurses identify and screen potentially eligible patients. The screening process includes the measurement of the screening pain score, using either the VAS or WBF-PRS, which must fall within the acceptable trial range. The unique participant screening form records reasons for non-randomisation where appropriate.

### Consent

Eligible patients and their parent or legal guardian are given sufficient time to read a summary Patient Information Sheet (PIS), approved by the Research Ethics Committee (REC), which contains all essential information regarding the MAGPIE trial. After the participant has been offered the opportunity to ask further questions and agrees to participate, informed consent is taken by a member of the research team who will remain blinded to subsequent randomisation and treatment allocation. For patients under the age of 16 years, written informed consent is sought from the parent or legal guardian, with verbal assent from the patient. Competent 16 and 17 year olds provide their own written consent. At the time of discharge from the ED, a detailed PIS is provided, which has also been approved by the REC.

### Enrolment and randomisation

Randomisation sequences, stratified by age group (6–8 years, 9–11 years and 12 to < 18 years in a 2:2:1 ratio), are prepared by an independent statistician. Patients are randomised in the ratio of 1:1 to the active (methoxyflurane) or placebo group. The IMP is packaged according to the randomisation sequence prepared by the independent statistician.

Following consent, an unblinded member of the trial team enrols the patient to the trial using the Interactive Web Response System (IWRS). At enrolment, the participant is allocated the next randomisation number in the appropriate stratum. Treatment allocation as per the randomisation scheme is maintained by allocating IMP or placebo with the next sequential patient number.

### Trial treatments

Methoxyflurane (active treatment) or normal saline (placebo) are administered by inhalation via the hand-held Penthrox® inhaler, and are self-administered by the patient under the supervision of a research nurse who is trained in administration.

#### Active treatment

A 3-ml sample of methoxyflurane is vaporised in a Penthrox® inhaler. On finishing the dose, the patient can request a second inhaler containing a further 3-ml dose. The maximum dose administered is 6 ml of methoxyflurane. The composition of methoxyflurane is detailed in Table 1.

**Table 1 Tab1:** Composition of methoxyflurane

Investigational product	Function	Each 1 ml contains	Each 3 ml contains
Methoxyflurane	Active ingredient	99.9% w/w	99.9% w/w
Butylated hydroxytoluene	Antioxidant	0.01% w/w	0.01% w/w

Methoxyflurane is supplied as 3 ml of liquid in glass bottles in the IMP pack, and is stored below 30 °C.

#### Placebo

A 5-ml sample of commercially available sterile 0.9% sodium chloride (normal saline) for injection is loaded into the Penthrox® inhaler. The patient can request a second inhaler containing a further 5-ml dose. The maximum dose administered does not exceed 10 ml.

#### Penthrox® inhaler

The hand-held Penthrox® inhaler is a small, lightweight, disposable, cylindrical polyethylene device, approximately 15 cm long in a distinctive green colour, shaped like a large (green) whistle (Fig. 3).

**Fig. 3 Fig3:**
[figure not shown]
The Penthrox® inhaler

There is a dilutor hole at the mouthpiece end, which, when covered with the patient’s index finger, allows a higher concentration of treatment to be inhaled. The device contains a polypropylene S-shaped wick, which absorbs the liquid. An internal one-way valve allows air and vapour to be inhaled; this closes on expiration to prevent exhalations (containing a mixture of air, methoxyflurane and carbon dioxide) passing back through the wick. The inhaler is a single-patient use device, which prevents cross-contamination between patients, and can be easily disposed of after use.

To minimise environmental release of methoxyflurane, an activated carbon (AC) chamber is inserted into the aperture at the top of the inhaler. The AC adsorbs the exhaled methoxyflurane without causing any resistance to inhalation or expiration.

### Loading of the Penthrox® inhaler and blinding procedures

The unblinded investigator is responsible for loading and dispensing Penthrox® inhalers in such a way as to maintain the blinding for the treating clinician and the blinded research nurse. The key challenges for maintaining the blinding in the MAGPIE trial are the ability to distinguish between active IMP and placebo by the appearance of the container, volume of liquid administered and smell of methoxyflurane. The inhaler loading occurs in a closed area which is geographically separated both from the participant’s treatment area and the location of blinded research staff.

Each patient is allocated a pack containing two Penthrox® inhalers, each with an AC chamber attached, two containers of either methoxyflurane or sterile normal saline and four sealable plastic bags. Placebo packs include a container of methoxyflurane which is used for blinding (see next section). At enrolment, the assigned participant number (linked to the randomisation number) is entered on all pack labels. Packs are prepared by an independent pharmaceutical distributor.

Each Penthrox® inhaler is loaded by pouring the full contents of either one 3-ml bottle of methoxyflurane (active treatment) or one 5-ml ampoule of sterile normal saline (placebo) into the inhaler, in accordance with the treatment allocation of the patient. Different volumes of methoxyflurane and normal sodium chloride are used to minimise the weight difference because of the significant solution density difference between methoxyflurane and 0.9% sodium chloride.

The inhaler is placed in a plastic bag, which is sealed and weighed prior to being dispensed to blinded investigators. Before sealing the plastic bag containing a placebo inhaler, several drops of methoxyflurane are placed on the wristband of the placebo inhaler, so that it is not possible for participants or blinded investigators to distinguish between active IMP and placebo based on a masking smell upon opening the plastic bag.

A second identical inhaler is prepared using the same treatment allocation. This second inhaler is to be available if requested by the patient if they deem the first inhaler is no longer effective. The maximum dose administered does not exceed 6 ml of methoxyflurane (2 × 3 ml) or 10 ml of placebo (2 × 5 ml).

Allocation of investigators to blinded or unblinded processes is the responsibility of the site Principal Investigators; once allocated, these investigators may not switch roles for the duration of the trial.

### Administration of trial treatments

The research nurse provides training in the use of the device to the patient using a demonstration inhaler which contains no IMP and supports them in its use as necessary for the duration of IMP administration. Baseline vital signs (heart rate, blood pressure, respiratory rate and oxygen saturation) are measured along with an assessment of baseline sedation level using the University of Michigan Sedation Scale (UMSS) [20].

After randomisation, the baseline (time = 0) pain score is assessed, to ensure relative stability of pain intensity. If the baseline pain score has fallen outside the range of 60–80 mm on the VAS or 6–8 on the WBF-PRS, the patient is withdrawn from the trial (randomised but not treated).

If successfully randomised, the research nurse assists the participant to self-administer 10 successive inhalations of the IMP. Participants and parents/legal guardians are advised that rescue analgesia is available immediately on request at any time. Permitted rescue medications are intranasal fentanyl, intranasal diamorphine, intranasal ketamine, intravenous morphine, oral morphine or Entonox (50% nitrous oxide and 50% oxygen mixture), dependent on the standard practice of the participating site and at the discretion of the treating clinician. This approach is in line with current recommended practice [10] for the management of moderate to severe pain. Standard-of-care oral analgesic medications (paracetamol and ibuprofen) may be administered as concomitant medications alongside rescue medication. Participants who report pain relief due to IMP inhalation are advised to continue to self-administer additional inhalations, as required, during their ED attendance.

### Trial assessments

Participants are evaluated according to the schedule of events outlined in Fig. 1.

#### Pain scores

Pain intensity is re-assessed using the VAS or WBF-PRS at 5, 10, 15, 20 and 30 min after the start of inhalation of the trial treatment, and every 30 min thereafter until ED discharge. Additional unscheduled pain scores are assessed at the time of any other key events, such as during any injury treatment, prior to rescue medication administration, prior to premature trial withdrawal or just prior to ED discharge.

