### Trial participants

#### Inclusion criteria

The following inclusion criteria apply:Age ≥ 6 years to ≤ 17 years.Attending an ED following minor trauma.Pain scores (at screening and just prior to administration of study treatment) measuring between 60 and 80 mm on the Visual Analogue Scale (VAS) [19] or, where the patient is unable to understand the VAS, pain scores between 6 and 8 using the Wong-Baker FACES® Pain Rating scale (WBF-PRS).

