### Primary outcome

The primary outcome is the change in VAS (including WBF-PRS scores subsequently converted to VAS values) at 15 min after the commencement of treatment.

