#### Statistical analysis plan

The primary analysis shall be an intention-to-treat (ITT) analysis of the difference between methoxyflurane and placebo on the VAS, to include all patients who are randomised and receive trial treatment and undergo at least one post-baseline efficacy assessment. A pragmatic conversion of WBF-PRS scores to VAS scores (e.g. WBF-PRS 2 = VAS 20 mm, WBF-PRS 4 = VAS 40 mm, etc.) will be completed. The primary model will be an analysis of covariance (ANCOVA) of the VAS at 15 min following the start of inhalation of trial treatment with baseline pain as covariate, treatment and age group as fixed effect and site as random effect using the ITT population. The treatment effect shall be estimated as the average difference between the methoxyflurane-treated group and the placebo group at 15 min. Pain scores taken after the initiation of a rescue medication will be included in the primary analysis. This approach is conservative for the primary analysis and allows for patients with missing data at any time point to be included in the analysis with less bias than if patients are dropped from the analysis. Sensitivity analysis of primary endpoint pain values shall be performed using Worst Observation Carried Forward (WOCF). To exclude the possibility that conversion of any WBF-PRS scores (ordinal scale) into VAS scores (continuous scale) significantly influences the outcome of the trial, sensitivity analysis using a non-parametric test (Wilcoxon rank-sum test) will be performed.

Various methods will be used for secondary endpoint analyses. For treatment comparison of change from baseline for continuous variables with more than one measurement within a time period, repeated-measures analysis employing restricted maximum likelihood (REML)-based mixed-model repeated measures (MMRM) will be used. For continuous variables with baseline value and one post-baseline measurement, ANCOVA will be used, unless specified otherwise. Least square means (LSmeans), SE, LSmeans difference, 95% confidence interval (CI) and *p*-value will be presented. Logistic regression analyses adjusted for baseline will be performed for the binary variables, and the odds ratio and 95% CI for the odds ratio of treatment group comparisons will be given.

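### The primary ANCOVA pools converted faces scores and true VAS scores with no term for the pain tool, at a small cost in precision and none in bias.

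*Protocol article*

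**What the plan says.** The Inclusion criteria make the VAS the default and allow the faces scale "where the patient is unable to understand the VAS". The Screening section then has the entry score taken "using either the VAS or WBF-PRS, which must fall within the acceptable trial range", and Enrolment and randomisation follows consent, so the screening tool is fixed before allocation. The time-0 score is taken after randomisation but before treatment, against the "range of 60–80 mm on the VAS or 6–8 on the WBF-PRS". Later scores are covered under Pain scores: "Pain intensity is re-assessed using the VAS or WBF-PRS at 5, 10, 15, 20 and 30 min after the start of inhalation".

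The Primary outcome is the "change in VAS (including WBF-PRS scores subsequently converted to VAS values) at 15 min after the commencement of treatment". The Statistical analysis plan section gives the conversion by example: "A pragmatic conversion of WBF-PRS scores to VAS scores (e.g. WBF-PRS 2 = VAS 20 mm, WBF-PRS 4 = VAS 40 mm, etc". It lists the terms of the primary model as an ANCOVA of the 15-minute score "with baseline pain as covariate, treatment and age group as fixed effect and site as random effect using the ITT population". To guard against an effect of the conversion on the result, it adds a Wilcoxon rank-sum test as a sensitivity analysis.

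**The concern.** The outcome variable is a mixture of two instruments. If children on the faces scale and children on the VAS differ in mean score at 15 minutes for a given age band, site and baseline, that difference sits in the residual. The tool is a pre-randomisation characteristic, and staff must know which tool produced each score or the conversion could not be made. It is therefore a covariate that is available at almost no cost and is not used.

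The article recognises that pooling the scales might matter, but the check it plans does not address this. A rank-sum test relaxes the assumption about the shape of the distribution. It still ranks converted faces scores, which fall on 20 mm steps if the scale runs in twos as the conversion examples imply, in one list with continuous VAS scores. It neither adjusts for the tool nor reports by tool. At stake is some precision in the primary estimate, and a clear answer to the article's own question about the two scales.

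**Working it through.** **Inputs from the article (Sample size estimation, Enrolment and randomisation):** 110 evaluable patients per arm, 1:1 allocation, difference 13.3 mm, pooled SD 27.1 mm, SD 28 mm in younger children and 22.5 mm in adolescents, age mix 40%/40%/20%, power at least 95%. The significance level is not stated; two-sided 0.05 is assumed.

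**Step 1: the stated power.** The standard error is 27.1 × √(2/110) = 3.654 mm. Then 13.3/3.654 = 3.640, and Φ(3.640 − 1.960) = Φ(1.680) = 95.3% (95.2% with the noncentral t on 218 degrees of freedom). For 95% power, 108 per arm are needed, against 110 planned. The figure reproduces.

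**Step 2: variance attributable to the tool within age band.** Let w be the share of patients in a band, p the share of that band on WBF-PRS, and D the mean difference between tools within band after the other model terms. The variance a tool term can remove is D² × Σ w·p·(1 − p).

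The article gives neither p nor D, so both are assumed. With p = 0.70, 0.30 and 0.05 for ages 6–8, 9–11 and 12–17:

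Σ = 0.4 × 0.21 + 0.4 × 0.21 + 0.2 × 0.0475 = 0.1775.

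The reference variance from the age-specific SDs is 0.8 × 28² + 0.2 × 22.5² = 627.2 + 101.25 = 728.45 mm². (The stated SD gives 27.1² = 734.41 mm², which makes no practical difference.)

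| Assumed D | Variance removed | Share of 728.45 | Equivalent patients of 220 | Power with 27.1² reduced by that amount |
|---|---|---|---|---|
| 5 mm | 4.4 mm² | 0.6% | 1.3 | 95.5% |
| 10 mm | 17.8 mm² | 2.4% | 5.4 | 95.8% |
| 20 mm | 71.0 mm² | 9.7% | 21.4 | 96.9% |

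This calculation is within band, so it already allows for the age-group term.

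**Step 3: how far the assumed shares matter.** The sum Σ w·p·(1 − p) cannot exceed 0.25, reached when half of every band uses each tool. At that ceiling, 5 mm gives 6.25/728.45 = 0.9%, 10 mm gives 25/728.45 = 3.4% and 20 mm gives 100/728.45 = 13.7%. Ignoring age bands and varying the overall WBF-PRS share from 10% to 50% with D from 5 to 20 mm, the residual SD falls from 27.1 to between 27.06 and 25.19 mm, and power rises from 95.3% to between 95.4% and 97.5%.

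**Step 4: the price of the term.** One extra parameter among 220 patients costs roughly 1/220 = 0.5% of the information. At D = 5 mm, gain and cost about cancel; at 10 mm there is a net gain of around 2%.

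**Step 5: bias.** The screening tool precedes allocation, so in expectation its distribution is the same in both arms. Leaving it out of a linear model therefore does not shift the expected treatment difference.

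**The case against.** The strongest reply is that this is a choice of covariate and not an error. Randomisation protects the estimate and the power calculation stands. Baseline pain and age group are already in the model, and inability to understand the VAS plausibly falls with age, so age group should absorb part of any tool effect. Eligibility holds both tools to the same 60–80 mm window at time 0. An offset of 20 mm within age band after all that would be extreme. The article's remark about the conversion concerns an ordinal scale treated as continuous, and does not assert that the tools differ in mean. All of this stands, and it is why the point is small. What remains is that the article lists the primary model's terms, the tool is not among them, and the rank-sum test does not fill the gap.

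A reader might infer something stronger from the Pain scores section: that staff may choose either tool at each time point, that children made drowsy by active treatment would be moved to the faces scale, and that the primary difference is therefore biased. The documents do not support this. That sentence names the trial's two tools, as the Screening and baseline text does. The Inclusion criteria tie the choice to the child's ability, which is unlikely to change in 15 minutes. Switching is not ruled out, but it is not permitted either, and a same-tool instruction is operational detail that an article may leave to the full protocol. No passage mentions changing tool, for drowsiness or any other reason. Any figure for such a bias would be the product of an excess of switching and an offset between tools, neither of which the article gives.

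**Conclusion.** The point holds as a modest improvement to the primary model. The planned ANCOVA leaves any between-tool difference in the residual although the tool is known before randomisation, and the planned sensitivity analysis does not separate the tools. The loss is one of precision: about 0.6% to 2.4% of the residual variance for an offset of 5 to 10 mm, worth some 1 to 5 of 220 patients, and 9.7% (about 21 patients) only at 20 mm. These sizes rest wholly on assumed tool shares and offsets. If the tools agree on average within age band, there is nothing to gain.

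It would be wrong to conclude that the treatment estimate is biased or that the trial is underpowered for this reason: the stated power reproduces at 95.3% without the term.

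**What to change.** In the Statistical analysis plan section, add the tool used at screening (VAS or WBF-PRS) as a fixed effect in the primary ANCOVA, and in the MMRM for consistency. The screening tool is the right version because it is fixed before allocation, whereas the time-0 score is taken afterwards. The cost is one degree of freedom and no new data collection. The change should be made before unblinding.

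As a clarification only, confirm in the full protocol that each child keeps the same tool from screening onwards, and say so under Pain scores. If a score is nevertheless taken on the other tool, flag it and examine it in a sensitivity analysis. It should not be discarded: that would turn an observed primary value into a missing one, against the inclusive approach the article takes to pain scores in the primary analysis.

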#### Vital signs and sedation scores

Vital signs (heart rate, blood pressure, respiratory rate and oxygen saturation) and UMSS are re-assessed at 5, 10, 15, 20 and 30 min after the start of inhalation of the trial treatment, and every 30 min thereafter until ED discharge.

#### Other key events

The following events are recorded if and when they occur:Treatment of the patient’s injury, and the start and end times of such treatment.Timing and nature of any AEs (other than those associated with the underlying minor trauma) and any associated change in trial treatment administration.Concomitant medication administration.

#### Global medication performance

Following completion of trial treatment administration, the patient, research nurse and treating clinician are each asked to rate the global medication performance on a 5-point Likert scale (poor, fair, good, very good, excellent).

### Events at the point of ED discharge

Upon completion of trial treatment administration, all inhalers are collected, placed and sealed in the plastic bags and returned to the unblinded investigator, who weighs the inhalers inside their sealed plastic bags and records the weights following trial treatment administration.

At the point of discharge, a final pain score and vital signs are recorded. For patients requiring inpatient admission, the time of such a decision to admit should be considered the discharge time in terms of trial activity. The final injury diagnosis is documented. A single dose of oral analgesia (paracetamol and ibuprofen) is offered to all patients unless these have previously been administered or are contra-indicated. In the case of patients who are being discharged home, rather than admitted, instructions are provided to the patient/parent on suitable analgesia post discharge (as per standard practice of participating sites). The patient/parent is provided with a diary card and asked to record all concomitant medications and any symptoms experienced from the time of discharge until the follow-up telephone call. The patient/parent is advised to contact the named trial doctor or research nurse in the event of any significant adverse event (SAE), using the contact information provided on the PIS. In any cases of SAE, the patient is recalled to the site for further assessment.

### Follow-up

At 14 ± 2 days after discharge from the ED, the research nurse telephones the patient/parent for safety follow-up. A set questionnaire is used, and the patient/parent is asked to refer to the information collated on their diary card. The following points are covered during the telephone call:Any concomitant medication(s) (name and dose of medication) taken since discharge.Any AE, other than those related to the original injury.Presence or absence of specific symptoms and signs, including those relating to potential nephrotoxicity and hepatotoxicity.In any cases of significant AE, the patient is recalled to the site for further assessment.

At least three attempts are made to contact the patient to collect this follow-up information. If the three attempts are unsuccessful, the patient’s general practitioner is contacted for information on any recent medical consultations.

